## Abstract

**Background:** Despite strong guideline recommendations, participation in cardiac rehabilitation (CR) among patients with chronic heart failure (CHF) remains low due to logistical, geographical, and psychosocial barriers. Telerehabilitation may help overcome these limitations by offering remote, structured exercise programs supported by digital technologies. **Objective:** The TELEREHAB-HF study aims to evaluate the efficacy of an 8-week, home-based cardiac telerehabilitation program compared to standard in-person rehabilitation in patients with CHF. **Methods:** This is a prospective, controlled cohort study involving 220 adult patients with CHF (NYHA class I–III) clinically stable and on optimized therapy. Participants are assigned to either a telerehabilitation group (remote CR via a digital platform with wearable sensors and real-time physiotherapist supervision) or a standard in-person rehabilitation group. The primary outcome is the change in peak oxygen uptake (VO_2_max) at 8 weeks. Secondary outcomes include quality of life, functional performance, biochemical and echocardiographic parameters, and cognitive function, assessed at baseline and at 4, 8, 16, and 24 weeks. **Expected Results**: We hypothesize that telerehabilitation will be non-inferior to standard CR in improving functional capacity and secondary outcomes, with additional benefits in accessibility and adherence. Data from remote monitoring may also support a translational “rehabilomics” approach to exploring exercise-induced biomarker changes. **Conclusions:** This study seeks to assess the clinical effectiveness, safety, and feasibility of a home-based telerehabilitation model for CHF, with the goal of informing future strategies for broader implementation and personalized rehabilitation. Trial Registration: ClinicalTrials.gov Identifier: NCT07023536

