This protocol describes a prospective, controlled study designed to evaluate the efficacy of an 8-week home-based cardiac telerehabilitation program, supported by real-time remote monitoring technologies, in patients with CHF. The primary objective is to assess improvements in exercise capacity, measured via peak oxygen uptake (VO_2_max), compared to standard in-hospital rehabilitation. Secondary outcomes will include biochemical, functional, and QoL measures.

In addition, the study adopts a translational and “rehabilomic” perspective, aiming to explore the role of exercise as a modulator of specific molecular pathways involved in heart failure [19,20]. By identifying circulating biomarkers that are both pathophysiologically relevant and potentially responsive to physical training, the study seeks to contribute to the development of personalized rehabilitation strategies and a deeper molecular characterization of CHF patients [21].

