## 8. Outcomes

Both groups will undergo standardized assessments at baseline (T0), mid-treatment (4 weeks, T1), post-treatment (8 weeks, T2), and at follow-up timepoints (16 weeks, T3; 24 weeks, T4). Evaluations will include cardiopulmonary functional performance, echocardiographic measurements, biochemical markers, cognitive function, and QoL (Table 3).

The primary outcome of the study is the improvement in functional capacity, assessed as a ≥10% increase in VO_2_max, measured via CPET at 8 weeks (T2).

Secondary outcomes include:QoL: Assessed using the KCCQ-12 and SF-36 at each timepoint.Biochemical parameters: Changes in BNP, NT-proBNP, creatinine, eGFR, serum electrolytes (sodium, potassium, chloride), glucose, and lipid profile.Functional assessments: Performance on the 6MWT and SPPB.Cognitive status: Assessed with the MMSE.Echocardiographic parameters: Left ventricular ejection fraction (LVEF), diastolic function indices (E/A—Ratio of early E to late A ventricular filling velocities; E/e’—Ratio of early transmitral flow velocity to early diastolic mitral annular velocity), and right ventricular function (TAPSE—Tricuspid Annular Plane Systolic Excursion, RVs’—Right Ventricular Systolic Velocity).Adverse events: Monitoring of any complications related to training or telemonitoring (e.g., hypotension, arrhythmias, device issues).

These outcome measures will allow for a comprehensive and longitudinal evaluation of the effects of both in-person and telehealth cardiac rehabilitation on patients with chronic heart failure.

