## 9. Statistical Analysis

### 9.1. Primary Endpoint Analysis

To evaluate the primary endpoint of the study—defined as a ≥10% improvement in VO_2_max at 8 weeks—paired comparisons between baseline and post-intervention values will be performed using a paired t-test for normally distributed data [36,37,38]. For non-normally distributed data, the Wilcoxon Signed-Rank test will be applied. Additionally, the proportion of patients achieving the predefined VO_2_max improvement threshold will be analyzed using logistic regression, with “Rehabilitation Type (Telerehabilitation vs. Standard)” as the main predictor. The model will be adjusted for clinically relevant covariates identified through baseline comparisons using ANOVA or chi-square tests. Odds ratios and 90% confidence intervals will be reported.

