## 10. Expected Results

We expect to observe that the telerehabilitation group will demonstrate a significant improvement in functional capacity, as evidenced by a ≥10% increase in VO_2_max after 8 weeks of intervention, compared to the standard in-person rehabilitation group. This improvement is expected to be sustained at 24 weeks, indicating the long-term efficacy of the program. Furthermore, we expect to observe positive trends in secondary outcomes, including enhanced QoL (as measured by KCCQ-12 and SF-36), improved functional performance (6MWT, SPPB), and favorable changes in biochemical markers (BNP, NT-proBNP, creatinine, and electrolytes).

In the telerehabilitation group, the use of real-time monitoring and personalized feedback is also expected to improve adherence and safety, with a low incidence of adverse events. Additionally, we anticipate that echocardiographic parameters, such as LVEF and diastolic function indices (E/A, E/e’), will show measurable improvement or stabilization.

Overall, the study is expected to demonstrate that a structured, telerehabilitation program is not only clinically effective and safe, but also a feasible and scalable alternative to traditional CR for patients with CHF.

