Cool-down (10 min)	- 5 min stretching scapular/pelvic muscles - 5 min breathing with Khymeia spirometer	- 5 min stretching scapular/pelvic muscles - 5 min breathing with volumetric incentive spirometer

**Table 3 healthcare-13-02074-t003:** Outcome Measures by Timepoint.

Outcome Type	Outcome Measure	Unit of Measure	Domain	Clinical Relevance/Rationale	T0 (Baseline)	T1 (4 wks)	T2 (8 wks)	T3 (12 wks)	T4 (24 wks)
Primary	≥10% improvement in VO_2_max (CPET)	mL/kg/min	Functional Capacity	Gold standard for evaluating aerobic capacity and predicting prognosis in CHF	✔		✔	✔	✔
Secondary	Change in body weight	Kg	Anthropometric	Important for monitoring nutritional status; weight fluctuations are clinically relevant predictors of CHF decompensation.	✔	✔	✔	✔	✔
Secondary	Change in BMI	kg/m^2^	Anthropometric	Static measure to stratify overweight, obesity, which may influence exercise response and prognosis in CHF	✔	✔	✔	✔	✔
Secondary	Change in KCCQ-12 Score	Points (0–100)	QoL	CHF-specific QoL instrument sensitive to clinical changes	✔	✔	✔	✔	✔
Secondary	Change in SF-36 Score	Points (0–100)	QoL	Generic QoL questionnaire for broader health-related QoL	✔	✔	✔	✔	✔
Secondary	Change in 6MWT	Meters	Functional	Test of submaximal exercise capacity; reflects improvements in daily functional status	✔	✔	✔	✔	✔
Secondary	Change in SPPB Score	Points (0–12)	Functional	Assesses lower extremity strength, balance, and mobility—predictive of disability and frailty	✔	✔	✔	✔	✔
Secondary	Change in MMSE	points (0–30)	Cognitive	Screens for cognitive impairment, which can affect adherence and prognosis in CHF patients.	✔	✔	✔	✔	✔
Secondary	Change in BNP	pg/mL	Biochemical	Established biomarkers of myocardial stress; reflect CHF severity and response to therapy.	✔		✔	✔	✔
Secondary	Change in NT-proBNP	pg/mL	Biochemical	Established biomarkers of myocardial stress; reflect CHF severity and response to therapy.	✔		✔	✔	✔
Secondary	Change in Serum Creatinine	mg/dL	Biochemical	Monitor renal function, critical in CHF management due to cardiorenal interactions and therapy impact	✔		✔	✔	✔
Secondary	Change in eGFR	mL/min/1.73 m^2^	Biochemical	Monitor renal function, critical in CHF management due to cardiorenal interactions and therapy impact	✔		✔	✔	✔
Secondary	Change in Serum Sodium	mmol/L	Biochemical	Important for assessing treatment safety (e.g., diuretics, ACE inhibitors) and arrhythmic risk	✔		✔	✔	✔

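### The primary outcome is the change in VO2max in the Abstract but a ≥10% increase in Sections 8 and 9.1 and Table 3, and Section 9.1 tests both without saying which decides the trial

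*Protocol article*

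**What the plan says.** All references are to the protocol article.

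- **Abstract (Methods):** "The primary outcome is the change in peak oxygen uptake (VO_2_max) at 8 weeks". No threshold is given.
- **Section 1, Background:** "The primary objective is to assess improvements in exercise capacity, measured via peak oxygen uptake (VO_2_max), compared to standard in-hospital rehabilitation". Again there is no threshold, and the comparison is between arms.
- **Section 8, Outcomes:** "The primary outcome of the study is the improvement in functional capacity, assessed as a ≥10% increase in VO_2_max, measured via CPET at 8 weeks".
- **Table 3:** the primary row reads "≥10% improvement in VO_2_max (CPET"), yet its unit is mL/kg/min, which is neither a percentage nor a yes/no unit.
- **Section 9.1, Primary Endpoint Analysis:** opens by defining the endpoint with the same 10% criterion. It then says that "paired comparisons between baseline and post-intervention values will be performed using a paired t-test for normally distributed data", with the Wilcoxon signed-rank test as the non-normal alternative. As an addition, "the proportion of patients achieving the predefined VO_2_max improvement threshold will be analyzed using logistic regression", with rehabilitation type as main predictor and covariate adjustment.
- **Section 9.3:** assumes a 10% rise in VO2max in the intervention arm relative to control, two-sided alpha 0.05 and 90% power. It arrives at 200 patients, or 220 after a 10% dropout allowance. No SD, responder rate or allocation ratio is stated.

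**The concern.** A change in VO2max and a ≥10% increase share the same measurement and the same week, but they are different endpoints. The first is summarised by a difference in means, the second by a difference in proportions or an odds ratio. The Abstract and the objective point to the first; Section 8, Section 9.1 and Table 3 point to the second.

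Section 9.1 should settle this, but it puts a test of each version under the primary heading and ranks neither. The two tests also answer different questions. The paired test compares baseline with week 8 and says nothing about telerehabilitation against in-person rehabilitation; only the logistic model compares the arms. So the version announced in the Abstract has no between-arm analysis in Section 9.1, and the version that has one is introduced there as an addition.

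At stake is a choice that could be made after the data are seen, with either result reported as primary. Allocation follows patient preference and no blinding is described, so a fixed primary endpoint is one of the few safeguards left.

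**Working it through.** **1. The definitions side by side**

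| Place | What is primary | Threshold | Comparison |
|---|---|---|---|
| Abstract | change in VO2max, week 8 | none | not stated in that sentence |
| Section 1 | improvement in VO2max | none | between arms |
| Section 8, Table 3 | increase in VO2max | ≥10% | not stated |
| Section 9.1, paired test | VO2max values | none | within group, before and after |
| Section 9.1, logistic model | proportion reaching threshold | ≥10% | between arms |
| Section 9.3 | 10% increase | scale not stated | between arms |

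No sentence says which of the two Section 9.1 results decides the trial. This finding needs no arithmetic.

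**2. Can the sample size show which endpoint was meant?**

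The 200 cannot be reproduced, because the SD or the responder rates are missing. I take 1:1 allocation (an assumption), two-sided 0.05 and 90% power, so z = 1.960 and 1.282.

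- *Read as a 10-point difference in mean percent change:* n per arm = 2(1.960 + 1.282)² × (SD/10)². The total is 44, 96, 170, 200, 264 and 380 for SD 10, 15, 20, 21.8, 25 and 30. The stated 200 corresponds to an SD of about 21.8 points.
- *Read as a 10-percentage-point difference in responders:* n per arm = [1.960√(2p̄(1−p̄)) + 1.282√(p₁(1−p₁) + p₂(1−p₂))]² / 0.10². For 40% against 50%, this is (1.379 + 0.897)² / 0.01 ≈ 518, which rounds up to 519 per arm, or 1038 in total. Over control rates of 10% to 80% the total runs from 532 to 1038.

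Section 9.3 is therefore compatible with a mean-difference reading at one particular SD. It does not fit a 10-point responder difference. A responder comparison with 100 per arm needs a difference of about 15 to 23 percentage points for 90% power. The text does not say which scale was used.

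**3. Illustration: the same true effect under both endpoints**

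Assumptions: 100 evaluable per arm, normal percent change with equal SD, two-sided 0.05, superiority.

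- A two-sample t-test has 90% power at a standardised difference d = 0.461.
- For control responder rate p_c, set c = Φ⁻¹(1 − p_c). The other arm's rate is then 1 − Φ(c − d).
- Power = Φ{[(p_t − p_c) − 1.960·SE₀] / SE₁}, with SE₀ pooled and SE₁ unpooled.
- Example at p_c = 0.50: p_t = 0.678, SE₀ = 0.0696, SE₁ = 0.0684. Power = Φ[(0.1775 − 0.1364)/0.0684] = Φ(0.60) ≈ 0.73.

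| Control responders | Other arm | Power, responder comparison |
|---|---|---|
| 20% | 35% | 67% |
| 30% | 47% | 72% |
| 40% | 58% | 73% |
| 50% | 68% | 73% |
| 60% | 76% | 70% |
| 70% | 84% | 64% |
| 80% | 90% | 54% |

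**4. Illustration: how often the two versions disagree**

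Simulation, 20,000 trials per setting, SD 21.8, control mean change 0%, 5% or 10%. Both versions are tested between arms: a t-test of mean change and a z test of responders. With a true difference of 10 points, they disagree on significance at 0.05 in 18% to 20% of trials. With no true difference, at least one is significant in 8.0% to 8.5% of trials, against roughly 5% to 6% for either alone.

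**The case against.** The strongest reply is that the operative text has one definition. Section 8, Section 9.1 and Table 3 all give the 10% criterion, and Section 9.1 states it expressly as the definition. The Abstract names the variable and could be leaving the threshold to the body, as abstracts do. The only between-arm primary analysis in the text is the responder model, so one might say the plan has already chosen.

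Most of this stands as a reading of the definition: on the text, the 10% criterion has the better claim. It does not settle the analysis. The same section that defines the responder endpoint tests the undichotomised values first and adds the responder model second, and Section 1 states the objective without a threshold.

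Three stronger readings are tempting, and the document does not support them.

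- *Section 10 as a third definition.* It expects an improvement "as evidenced by a ≥10% increase in VO_2_max after 8 weeks of intervention, compared to the standard in-person rehabilitation group", which can be read as a 10% gap between arms. But it is a statement of expected results, not an endpoint definition.
- *A power loss of 17 to 36 points caused by the inconsistency.* That is 90 − 73 and 90 − 54 in the table above. The comparator is a between-arm t-test that Section 9.1 does not plan. The calculation also ignores covariate adjustment and the non-inferiority hypothesis in the Abstract, and assumes equal arms although patients choose their arm. It shows what dichotomising can cost, not a measured loss in this trial.
- *The responder endpoint is itself wrong.* Losing information at a cut-point is a property of any responder endpoint. A sponsor may accept it; that is a preference, not an error.

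**Conclusion.** The concern holds as an inconsistency in the definition, together with an unranked primary analysis. The Abstract and Sections 8 and 9.1 with Table 3 do not name the same endpoint, Section 9.1 carries both into the primary analysis, and Section 9.3 does not show which one the trial was sized for. None of this depends on an assumed figure.

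The consequence can only be illustrated. Under normality, equal SD, 1:1 allocation and superiority, a setting with 90% power for means gives about 54% to 73% for the responder comparison. Being free to claim whichever between-arm result is significant raises the false-positive rate to about 8%. That last figure applies only if a between-arm test of change were brought in to serve the Abstract's outcome; the paired test now in Section 9.1 is not such a test.

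A reader might infer from step 2 that 200 patients is too few. The document does not support that: 200 is consistent with a mean difference at an SD near 21.8 points and cannot be judged until the scale is stated.

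**What to change.** Name one primary endpoint and one deciding between-arm analysis, and bring the Abstract, Section 8, Section 9.1, Section 9.3 and Table 3 (including its unit) into line before the data are analysed. Either of two routes works.

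1. **Keep the ≥10% responder endpoint.** Make the adjusted logistic model the deciding analysis, correct the Abstract, and list the continuous change as secondary. This is the smaller edit.
2. **Make the between-arm difference in VO2max change primary**, adjusted for baseline VO2max, with the ≥10% proportion as a named secondary outcome. The small downside is that the responder result loses primary status.

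On either route, label the paired within-group test as supportive only. Restate the sample size on the chosen scale, giving the SD or the two responder rates and the assumed allocation ratio.

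The cost is wording in the protocol and, where it differs, the registration. CPET is already scheduled at baseline and week 8, so the alignment needs no new data. Restating the sample size may show that 200 gives less than 90% power on the chosen scale; that is better known now than at analysis.

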The collected clinical and biometric data will contribute to a translational and “rehabilomics” [17,18] framework, aiming to explore the impact of exercise on the molecular profile of CHF patients. Blood and urine samples will be collected and stored in a biobank for future analysis of biomarkers potentially modifiable by physical activity, thus supporting the identification of individualized rehabilitation strategies.

Patients in the control group (TELEREHABILITATION-NO) will follow a conventional 8-week hospital-based cardiac rehabilitation program under direct supervision. Sessions will be conducted at the outpatient cardiac rehabilitation facility and will include the same structure and intensity of exercise training as the intervention group. Vital signs and effort perception will be assessed and recorded manually using standard clinical tools.

All patients, regardless of group assignment, will undergo standardized evaluations at baseline, and at 4, 8, 16, and 24 weeks.

Prior to the intervention, each participant will undergo a comprehensive clinical evaluation performed by a cardiologist specialized in cardiac rehabilitation—who also serves as the head of the Cardiac Rehabilitation Unit at AOU “San Giovanni di Dio e Ruggi d’Aragona” in Salerno—including clinical examination, ECG, transthoracic echocardiography, and cardiopulmonary exercise testing (CPET) [22,23].

In parallel, physiotherapists will conduct a set of standardized functional assessments, including: 6-Minute Walk Test (6MWT), Short Physical Performance Battery (SPPB), Mini-Mental State Examination (MMSE) for cognitive screening, administration of health-related quality of life (HRQoL) questionnaires, including the Kansas City Cardiomyopathy Questionnaire—12 items (KCCQ-12) and the Short Form Health Survey—36 items (SF-36) [24,25,26,27].

This multidisciplinary assessment ensures that all participants are clinically stable, functionally and cognitively evaluated, and safely eligible to participate in either arm of the rehabilitation program.

Subsequent assessments will include laboratory analyses, including B-type natriuretic peptide (BNP), N-terminal pro B-type natriuretic peptide (NT-proBNP), Serum creatinine, electrolytes (sodium, potassium, chloride), lipid profile, blood glucose.

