### 9.3. Sample Size Calculation

Based on the primary endpoint, the required sample size was calculated using G*Power software (Version 3.1.9.7). Assuming a 10% increase in VO_2_max in the intervention group compared to the control group, with a two-sided alpha level of 0.05 and statistical power (1–β) of 90%, the estimated sample size is 200 patients.

To compensate for a potential 10% dropout rate, the final target enrollment is 220 patients with CHF. This sample size is considered sufficient to detect clinically relevant differences in functional capacity and allows for robust evaluation of secondary outcomes including QoL, echocardiographic and biochemical parameters.

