## 11. Discussion

The results of this study are expected to add to the existing evidence base regarding the use of telerehabilitation as a potential alternative to traditional center-based cardiac rehabilitation in patients with CHF. Observed improvements in functional capacity (VO_2_max), along with changes in QoL, functional performance, and selected biochemical and echocardiographic parameters, may help further clarify the role of exercise-based rehabilitation—whether delivered in-person or remotely—as part of comprehensive heart failure management.

Telerehabilitation presents certain advantages, such as increased accessibility, fewer logistical constraints, and the possibility of enhancing adherence through remote monitoring and real-time feedback [11,39]. These features may be particularly beneficial for individuals with limited mobility, transportation challenges, or those living in underserved or rural settings [40,41,42,43,44]. The use of wearable sensors and a secure digital platform allows for continuous monitoring and adjustment of exercise intensity, potentially supporting safety and protocol adherence. Should outcomes in the telerehabilitation group be comparable to, or better than, those of standard care, this could inform future considerations regarding its broader implementation and integration into healthcare systems seeking to optimize resource use and reduce hospital readmissions. A low rate of adverse events, coupled with satisfactory levels of patient engagement, may further support its feasibility.

Nonetheless, the study recognizes potential challenges, including variability in digital literacy, differences in home settings, and unequal access to technology [45,46]. To address these, participants will receive initial in-person training and continued technical assistance. Future investigations will be necessary to assess long-term clinical outcomes and cost-effectiveness beyond the six-month observation period [9].

In conclusion, this study seeks to evaluate the safety, feasibility, and potential utility of telerehabilitation as a component of secondary prevention and CHF management, in alignment with current clinical guidelines and digital health strategies.

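### The abstract hypothesises non-inferiority, but the study is sized and described for superiority, with no margin or decision rule for a non-inferiority conclusion

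*Protocol article*

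**What the plan says.** - **Abstract, Expected Results:** "We hypothesize that telerehabilitation will be non-inferior to standard CR in improving functional capacity and secondary outcomes". The article mentions non-inferiority nowhere else. The objectives in the Abstract and in Section 1 only say that the two forms of rehabilitation are compared.
- **Section 9.3:** the calculation rests on "Assuming a 10% increase in VO_2_max in the intervention group compared to the control group". Alpha is 0.05, two-sided, and power is 90%. From this, "the estimated sample size is 200 patients", and "To compensate for a potential 10% dropout rate, the final target enrollment is 220 patients with CHF".
- **Section 9.1:** paired before-and-after tests, plus an adjusted logistic regression of the responder outcome on rehabilitation type, reported as odds ratios with 90% confidence intervals.
- **Section 9.2:** two-sided p < 0.05 as the significance criterion for all final analyses.
- **Section 10:** a significant improvement in the telerehabilitation group, "as evidenced by a ≥10% increase in VO_2_max after 8 weeks of intervention, compared to the standard in-person rehabilitation group".
- **Section 11:** a result that could inform wider implementation is introduced with "Should outcomes in the telerehabilitation group be comparable to, or better than, those of standard care".
- **Section 2:** in-person sessions "will include the same structure and intensity of exercise training as the intervention group".

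No section states a non-inferiority margin or says how the odds ratio interval would be judged.

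**The concern.** Non-inferiority and superiority need different null hypotheses, sample size inputs and decision rules. The article takes its hypothesis from one and its calculation, significance criterion and expected result from the other. The hypothesis that the reader is told is being tested is therefore not the one that the 200 patients were calculated for.

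This matters most for the conclusion that Section 11 would act on. The second half of that condition, a better result, can be reached by a significant difference. The first half, a comparable result, has no valid rule as written: a non-significant difference is not evidence of non-inferiority, and the interval has no margin to exclude. The Data Availability statement says that data collection is ongoing, and a margin chosen after outcomes have been seen would carry little weight.

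The equal exercise prescription in Section 2 points the same way. Two arms with the same training invite a non-inferiority question, and a 10% advantage for one of them is an optimistic planning assumption.

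**Working it through.** **Inputs from the article:** 200 evaluable patients, two-sided alpha 0.05, 90% power, a 10% increase compared with control, 10% dropout.

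**Inputs not given, assumed here:** 1:1 allocation (100 per arm; the article allocates by preference and logistics and gives no ratio), the SD, baseline VO2, responder rates and any margin. All figures are unadjusted for covariates or propensity score.

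**1. The plan's own figure.** The 200 cannot be reproduced, because Section 9.3 does not give the SD, the responder rates or the scale of the 10%. Solving backwards for the standardised difference:

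d = (1.960 + 1.282) × √(2/100) = 3.242 × 0.1414 = 0.458 SD.

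- As a 10-point difference in percentage change, this requires an SD of 10/0.458 = 21.8 points.
- As 10% of an assumed baseline of 15 mL/kg/min (a difference of 1.5), it requires an SD of 1.5/0.458 = 3.27. For that difference, the total N runs from 76 (SD 2) to 468 (SD 5).
- As a 10-point difference in responder rate, the total N is 376 to 1,038 for control rates from 5% to 80%, and 100 per arm gives 29% to 66% power. The 200 does not fit this reading.
- Dropout: 200/0.9 = 222.2, so 223 against 220 stated. The gap is immaterial.

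On every reading this is a calculation for detecting a difference between arms.

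**2. What 200 patients support for non-inferiority.** With a true difference of 0 and 90% power, the smallest margin is (z for 1 − alpha + 1.282) × standard error.

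| | One-sided 0.025 | One-sided 0.05 |
|---|---|---|
| Continuous, SE = √(2/100) = 0.1414 SD | 3.242 × 0.1414 = 0.458 SD | 2.927 × 0.1414 = 0.414 SD |
| Responders, 50% in both arms, SE = √(2 × 0.25/100) = 0.0707 | 3.242 × 0.0707 = 22.9 points | 2.927 × 0.0707 = 20.7 points |

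The 0.458 SD is the same number as in step 1: at one-sided 0.025, the margin would be as large as the whole effect that the study can detect with 90% power. An unequal split widens it. With 140 and 60 patients, for example, 3.242 × √(1/140 + 1/60) = 3.242 × 0.1543 = 0.50 SD.

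**3. Tighter margins** (illustrative, assumed; responders at 50% in both arms).

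| Margin | Power at 100 per arm, 0.025 / 0.05 | Evaluable N for 90% power, 0.025 / 0.05 |
|---|---|---|
| 10 points | 29% / 41% | 1,052 / 858 |
| 15 points | 56% / 68% | 468 / 382 |
| 20 points | 81% / 88% | 264 / 216 |
| Half the implied effect (0.229 SD) | 37% / 49% | 802 / 654 |

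**4. The planned interval.** With 50 responders and 50 non-responders observed in each arm, the unadjusted 90% interval for the odds ratio is exp(±1.645 × √(4/50)) = 0.63 to 1.59. The article offers nothing to judge the lower limit against. A 90% interval corresponds to one-sided 0.05, whereas two-sided 0.05 in Sections 9.2 and 9.3 corresponds to a 95% interval.

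**The case against.** **Non-inferiority may be a stray word.** It occurs once, in a forward-looking part of the abstract, while the body speaks of differences. That is a fair reading, and if it is right the repair is a deletion. The abstract would still state a hypothesis that the study was not sized for, so the passages must be reconciled either way.

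**A margin can be left to an analysis plan.** True of a condensed article, and a missing margin alone would not be a finding. What stands is the conflict within the article: the sample size, alpha and expected result printed here belong to a different question from the printed hypothesis. A later margin would not make Section 9.3 a non-inferiority calculation.

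**The 90% interval shows non-inferiority intent.** It may. It is the usual companion of a one-sided 5% non-inferiority test, so it would be wrong to say that Section 9 holds nothing but difference tests. The interval still lacks a margin and disagrees with the stated alpha.

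**Stronger readings that the article does not support.**
- A reader might infer that the authors will read a non-significant test as comparability. No section says so; Section 11 is conditional and names no test.
- A reader might infer that a relevant deficit would usually go undetected. That depends on the deficit chosen. At 100 per arm, an assumed deficit of 0.25 SD is missed 58% of the time (42% power), but one of 0.46 SD only about 10%. The article does not say which deficit is clinically relevant.
- A reader might infer that the equal prescription rules out an advantage. It does not: Section 10 expects better adherence from monitoring and feedback. The assumed effect is optimistic, not contradictory.

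**Conclusion.** The point stands as an inconsistency in the design as written. The hypothesis is non-inferiority; the calculation, significance criterion and expected result are those of superiority; and there is no valid rule for concluding that telerehabilitation is comparable.

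The study is not necessarily too small for non-inferiority. It would be adequate at 90% power only if a margin of about 0.41 to 0.46 SD, or about 21 to 23 percentage points on the responder scale, is clinically defensible, and the article makes no case for a margin of any size. These figures rest on an even split, a true difference of zero, 50% responders in both arms for the percentage-point figures, and no adjustment. The inconsistency itself rests on none of these assumptions.

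It should be resolved before outcomes are examined, because the choice determines the margin, the interval and the permitted conclusion.

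**What to change.** State one hypothesis in the abstract and in Sections 9 and 10.

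**If it is non-inferiority:**
1. Settle the primary endpoint first. The abstract names change in VO2, while Sections 8 and 9.1 use the responder outcome of at least 10%. The margin must be on the scale of whichever is declared.
2. Fix a margin now, with a clinical justification. Do not derive it from the 200 patients.
3. Use one confidence level that matches the stated alpha: 95% for one-sided 0.025, or 90% with one-sided 0.05 stated openly.
4. Conclude non-inferiority only if the adjusted interval excludes the margin, and test superiority only after that.
5. Replace the calculation in Section 9.3 with the non-inferiority power that 200 evaluable patients give for that margin, stating the SD or responder rates and the allocation ratio used. If it is below 90%, say so and limit the claim.

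**If it is superiority:** delete the non-inferiority wording from the abstract and state that a non-significant difference will not be read as comparability.

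**Cost:** wording and one recalculation. It cannot be promised that 200 patients will be enough; that depends on the margin. The downside is that the restated power may be below 90% for a clinically acceptable margin.
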